**Protocol S1**

**Full Title: Determination of the symptoms of aspartame in subjects who have reported symptoms in the past compared to controls: a pilot double blind placebo crossover study**

***Biochemical analysis will be undertaken in the clinical laboratories at Hull Royal Infirmary***

***Metabolomics will be undertaken by Imperial College, London***

**List of abbreviations and definitions**

**mg/kg bw – dose of aspartame in mg per kg bodyweight**

**EFSA – European Food Safety Authority**

**FSA – Food Standards Agency**

**Background information**

Prior research investigating the potential health effects of aspartame have been criticised by lobby groups as the work to date is not robust due to poor methodology or confounded as aspartame was not the main focus of the study. To prepare for a definitive study it is thought that a pilot study is necessary to prove the methodology, the preparation to be used and the acceptability of the study to the scientific community, food regulatory and other stakeholders. This will allow an extensive and comprehensive study to be powered appropriately.

This double blind pilot study aims to utilise a defined product, assess the efficacy of the necessary psychometric and biochemical methodologies to determine whether the perceived effects of aspartame can be detected in sufferers (of aspartame effects) compared to non suffers. This will allow the preparation of a full trial to be accurate in terms of endpoints studied, numbers of participants etc.

**Aims and Objectives**

To study the acute effects of aspartame on psychological symptoms, biochemistry and metabonomics.

To ascertain the optimal design for a larger study.

To validate that the product used for the trial is optimal and fit for purpose

To validate the questionnaire tools for the identification of symptoms of adverse events in individuals reporting self diagnosed adverse reactions.

To validate the biochemical assays in individuals reporting self diagnosed adverse reactions.

To determine the power needed for a large scale study for the investigation of subjects with self diagnosed adverse reactions to aspartame.

**Outcome:**

Confirm the robustness of the methodology for a definitive clinical trial.

**Study Design**

This is a double-blinded, placebo-controlled trial involving 50 self reported responders to aspartame (report that they have side effects when eating/ drinking products containing aspartame). Each participant will be given a single exposure to a bar containing aspartame as well as a matched placebo bar containing no aspartame. The dose of aspartame in the bars is 100mg, this is well below the Reference Daily Intake maximum recommended by EFSA of 40mg/kg body weight. In addition 25 participants with self-reported aspartame sensitivity and 25 matched control participants will be recruited to look at nocebo effect where they were given two lots of placebo (second part). The nocebo effect refers to the negative consequences of an inert treatment. The intention is to analyse the second part of the study only if any discriminating effect was observed between the two arms in the first part of the study.

*Plan for trial*

*Visit 1:*

Consent

Height, weight and waist measurements

Baseline bloods: full blood count and biochemical profile for safety

Baseline questionnaires of health and symptoms

- Beck depression inventory (BDI)
- Hospital Anxiety and Depression Scale (HADS)
- Trait anxiety perceived stress scale (STAI)
- Life events in last 5 years and 12 months (SRRS)
- Toronto Alexithymia scale
- Whiteley Index of Hypochondriasis

*Visit 2:*

Attend fasting

Fasting bloods: insulin, glucose, GLP1, GIP, biochemical profile and glucose

Give test or placebo challenge snack bar

Use of Visual Analogue Scales to assess effects of the aspartame/ placebo every 15 minutes for 2 hours, then at 3 hours and at 4 hours

Repeat bloods 4 hours following the consumption of the bar: insulin, glucose, GLP1, GIP, biochemical profile and glucose.

After lunch and recording of any adverse events or symptoms, subjects go home.

Telephone call 48 hours after visit to remind about questionnaires and monitor any side effects

One week between visits.

*Visit 3:*

Attend fasting

Fasting bloods: insulin, glucose, GLP1, GIP, biochemical profile and glucose

Give test or placebo challenge snack bar

Use of Visual Analogue Scales to assess effects of the aspartame/ placebo every 15 minutes for 2 hours then at 3 hours and at 4 hours

Repeat bloods 4 hours following the consumption of the bar: insulin, glucose, GLP1, GIP, biochemical profile and glucose.

Urine to be collected at the start of the study, at the end of the study (4 hours). If willing to do so, a urine sample will be requested at 12 hours and 24 hours: prepaid containers will be provided to post these back to the centre.

Imperial College, London will be subcontracted to measure aspartame and its breakdown products in blood and urine by the use of metabolite analysis using NMR and mass spectrometry. Samples will be sent to them in an anonymous manner to preserve confidentiality.

After lunch and recording of any adverse events or symptoms, subjects go home.

Telephone call 48 hours after visit to remind about questionnaires and monitor any side effects

*Criteria for discontinuation of individual subjects, parts of the study or the entire study*.

As it is a relatively short intervention with a well tolerated food stuff this is felt to be incredibly unlikely.

*Individuals may be withdrawn if:*

- If they lose capacity
- If they develop an allergy or adverse reaction to the aspartame or the ingredients in the bar
- If unable to eat less than 75% of the snack bar

For the part or the whole study to be withdrawn

- If the Food Standards Agency said that aspartame was unsafe as a food ingredient.

Plan for the Study

| Procedure | Visit 1 | Visit 2 | Visit 3 |
| --- | --- | --- | --- |
|  | Week 0 | Week2 | Week3 |
| Consent | X |  |  |
| Blood tests –   - full blood count - biochemical profile | X |  |  |
| - Baseline Questionnaires - Beck depression inventory (BDI) - Hospital Anxiety and Depression Scale (HADS) - Trait anxiety perceived stress scale (STAI) - Life events in last 5 years and 12 months (SRRS) - Toronto Alexithymia scale - Whiteley Index of Hypochondriasis | X |  |  |
| Height, weight and waist measurement | X |  |  |
| Fasting blood test-  Insulin, glucose, GLP1, GIP, biochemical profile and glucose |  | X | X |
| Feeding of snack bar, with or without aspartame |  | X | X |
| Completion of Visual Analogue Scale every 15 minutes for 2 hours |  | X | X |
| Blood test 4 hours after eating bar:  Insulin, glucose, GLP1, GIP, biochemical profile and glucose |  | X | X |
| Urine aliquot at baseline, 4, 12 and 24 hours after eating bar, |  | x | x |
| Giving of Speilburger State trait anxiety questionnaire and food symptom log |  | X | X |
| Reminder telephone call and review of symptoms, 48 hours after the test | X | X | X |

A schematic diagram of the trial design, procedures and stages (can be in a form of a table).

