**Subject selection**

This study has 2 groups of subjects, those who report having symptoms when consuming aspartame and those who consume aspartame with no ill effects.

The study will recruit 50 subjects in each group.

The responders will be approached by the lobby and interest groups who have accumulated a list of individuals who have an interest in aspartame and report side effects when consuming it. Information will be provided to these groups and a letter with a summary information sheet will be provided to these group to distribute amongst their members. Then the individuals who are interested in taking part in the study will contact the research department to arrange an appointment.

The healthy volunteers will be recruited via a poster and they will be encouraged to contact the research department for study information. The poster will be displayed in primary care centres, university buildings and within the hospital trust. Following subjects contacting the research centre, information will be sent out, following the receipt of the information subjects will be allowed to read the information and asked if interested in further participation in the study, if so a screening appointment will be arranged.

Number of centres involved:

One NHS site: Hull and East Yorkshire Hospitals NHS Trust

One Academic site: University of Hull

Over 1000 side effect reports have been collated by interest groups in the UK, therefore about 100 are likely to be from the Yorkshire region, therefore before requiring subjects to travel excessive distances about 50% of the local individuals who respond to aspartame will need to be recruited. The recruitment of healthy volunteers is not foreseen to be a problem as the organisations who will be displaying the posters employ over 10,000 people and have even greater numbers accessing their buildings every month.

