**Sample Size**

The ability to estimate an appropriate sample size for the pilot is not possible as there are no comparable studies for guidance. This pilot will allow the main study to be powered appropriately on a specific factor. However, Power and sample size for pilot studies has been reviewed by Birkett and Day (Birkett MA, Day SJ. Internal pilot studies for estimating sample size. Statistics in Medicine 1994; 13:2455-2263). They concluded that a minimum of 20 degrees-of-freedom was required to estimate effect size and variability. Hence, we intend to recruit 50 patients per group (75-105 maximum) allowing for drop-outs and covariate adjustment.

.

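### The protocol contradicts itself on who receives aspartame and on how many reporters and controls are recruited

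*Protocol*

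**What the plan says.** The protocol describes the participants and their bars in several places.

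- **Study Design, first part:** "This is a double-blinded, placebo-controlled trial involving 50 self reported responders to aspartame". The exposure follows directly: "Each participant will be given a single exposure to a bar containing aspartame as well as a matched placebo bar containing no aspartame". No control is named here.
- **Study Design, second part:** "In addition 25 participants with self-reported aspartame sensitivity and 25 matched control participants will be recruited to look at nocebo effect". Both of the bars that these people eat are placebo. The 25 controls are the only ones that this section mentions.
- **Subject selection:** two groups are defined, people who report symptoms and people who consume aspartame without ill effect. "The study will recruit 50 subjects in each group". On feasibility, from about 100 likely reporters in the region, "about 50% of the local individuals who respond to aspartame will need to be recruited".
- **Sample Size:** "we intend to recruit 50 patients per group (75-105 maximum) allowing for drop-outs and covariate adjustment".
- **Treatment of subjects, and Use of treatment within the trial:** subjects eat two bars a week apart, one with 100 mg aspartame and one without. Neither section makes an exception for a group or a part.
- **Randomisation:** one-to-one allocation to two treatment groups, with no placebo-placebo allocation mentioned.
- **Full title and Background information:** the effects of aspartame in reporters are to be compared with those in controls or non-sufferers.

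**The concern.** Site staff need to know which two bars a control receives, and the protocol gives two answers. In Study Design a control gets placebo twice. In the treatment sections every subject gets one bar of each kind.

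The choice decides whether the title question can be answered. A reporter-versus-control comparison of the aspartame effect needs an aspartame-minus-placebo difference in both groups, and controls who only ever eat placebo have none. Conversely, if everyone eats one bar of each kind, the nocebo part does not exist.

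The planned group sizes, the recruitment forecast and the number of bar packs to be coded at manufacture all depend on the same choice.

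**Working it through.** **1. The protocol's own total.** Subject selection and Sample Size give 2 × 50 = 100. Study Design gives 50 + 25 + 25 = 100. The stated totals agree.

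**2. Composition.**

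| Source | Reporters | Controls | Total |
|---|---|---|---|
| Study Design | 50 + 25 = 75 | 25 | 100 |
| Subject selection, Sample Size | 50 | 50 | 100 |
| Difference | 25 | 25 | 0 |

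Controls differ by a factor of two (50/25).

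**3. Who eats aspartame.**

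| Reading | Reporters exposed | Controls exposed |
|---|---|---|
| Study Design | 50 | 0 |
| Treatment sections applied to the groups in Subject selection | 50 | 50 |

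Applied to the people in Study Design, the treatment sections would expose all 100, including the 50 in the second part who are said to get placebo twice.

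**4. Can the title comparison be estimated?** Let D(R) be the mean aspartame-minus-placebo difference in reporters and D(C) the same in controls. The title comparison is D(R) − D(C). Under Study Design, D(R) comes from 50 reporters. Each control supplies only placebo minus placebo, so D(C) has no data and the contrast cannot be estimated at any sample size. Two things can still be estimated: D(R) itself, within reporters, and the difference in placebo response between 25 reporters and 25 controls.

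**5. The range of 75 to 105.** The parenthesis does not say whether it is a total or per group, and no drop-out rate is stated from which it could be derived.

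- Read as a total, 100 lies inside it.
- Read per group, it is a ceiling above an intended 50.
- Only if the 25 + 25 of the second part is added to a first part of 50 + 50 does the total become 50 + 50 + 25 + 25 = 150. That exceeds 105 by 45 if 105 is a total. If the range is per group, 75 per group sits at its lower end.

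**6. Does the 20-degrees-of-freedom rule settle it?** It needs 21 subjects for a paired analysis (21 − 1 = 20). A group of 50 gives 49, and even 25 controls give 24. The rule is met under every reading, so it cannot show which one was intended.

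**7. Local recruitment.** With about 100 local reporters, 50/100 = 50% matches Subject selection. Study Design needs 75/100 = 75%. Both figures are before exclusions and replacements.

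**The case against.** The best defence is that the totals do not conflict. Both descriptions come to 100, which lies within 75 to 105 read as a total. This stands, and it rules out a stronger reading. A reader might infer that the protocol sets totals of 100 and 150 against a maximum of 105, and so overshoots by 45. The documents do not support that. No section states 150. Subject selection as it reads gives 100, and it never says that its 50 per group belongs to the first part only. Nor is a per-group ceiling above 50 a contradiction in itself. A reader might also take the 5 places between 100 and 105 as too small an allowance for losses, but no drop-out rate is given to judge it by, and Withdrawal of Subjects provides for replacement where possible.

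The treatment sections could also be meant for the first part only. That would make room for the nocebo part, but neither section says so, and it would leave controls without aspartame and the title comparison without data.

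Three further limits are fair. Subject selection says nothing about bars, so a crossover in 50 reporters and 50 controls is an inference, not existing text. Aims and Objectives contains no reporter-versus-control comparison, so nothing there needs deleting. And the 50% local figure is a forecast of recruitment before long travel, from over 1000 reports nationally; it is not a limit on recruitment.

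None of this removes the conflict over exposure or over group sizes.

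**Conclusion.** The protocol is wrong as written on two linked points. Group sizes are 75 reporters and 25 controls in one place and 50 and 50 in others. The number of controls who eat aspartame is 0 in Study Design, and 50 if the treatment sections apply to the groups in Subject selection. Under Study Design the comparison in the title and Background cannot be estimated. The aspartame effect within reporters can be estimated under either reading.

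This rests on taking Study Design at its word: the second part consists of additional people, and the sentence on exposure to both bars refers to the 50 reporters just named.

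The unlabelled range in Sample Size and the 50% forecast are lesser defects. The forecast is out of line with Study Design by 25 reporters, or 25 percentage points of about 100 local reporters. The documents do not show which design was intended.

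**What to change.** Put one table in Study Design, of group by part by bar sequence, with a number in each cell. Reconcile Subject selection, Randomisation, Treatment of subjects, Use of treatment within the trial and Sample Size to it. The sponsor should state which design is meant:

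- **(a) Controls also take part in the aspartame and placebo crossover.** Say so in Study Design and state the resulting number per group and part. The total should follow from that decision; 150 should not be written in by default.
- **(b) Study Design is meant as it stands.** State 75 reporters and 25 controls in Subject selection and Sample Size. Limit the statement that subjects eat one bar of each kind to the first part. Reword the title and Background so that controls inform only the placebo (nocebo) comparison.

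In either case, say whether 75 to 105 is a total or per group and how it was obtained, and make the local recruitment percentage match the confirmed number of reporters.

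The reconciliation itself costs protocol wording. If 75 reporters are confirmed, the recruitment forecast becomes less favourable. Under (a), any enrolment beyond 100 would be a consequence of the sponsor's choice and should be stated as such.

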**Primary Endpoints**

**This is pilot study**

**The primary endpoint is the testing of the rigour of the study methods and design.** To determine the power needed for a large scale study for the investigation of subjects with self diagnosed adverse reactions to aspartame.

To study the acute effects of aspartame on psychological symptoms, biochemistry and metabonomics.

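### Analysing the placebo-placebo part only if the first part discriminates leaves its nocebo question unanswered in the case where nocebo is the leading explanation

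*Protocol*

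**What the plan says.** Protocol, Study Design, describes two parts. In the first, "This is a double-blinded, placebo-controlled trial involving 50 self reported responders to aspartame" are studied, and "Each participant will be given a single exposure to a bar containing aspartame as well as a matched placebo bar containing no aspartame". The section on blinding says that the bars are identical apart from the aspartame, and the section on use of treatment says that their order is randomised.

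The second part has different people: "In addition 25 participants with self-reported aspartame sensitivity and 25 matched control participants will be recruited to look at nocebo effect". They receive placebo on both occasions. The protocol explains the term: "The nocebo effect refers to the negative consequences of an inert treatment".

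The condition follows directly, worded as an intention: "analyse the second part of the study only if any discriminating effect was observed between the two arms in the first part". The protocol gives no reason for it, does not say which arms or which effect are meant, and makes no provision for the second part after a null first part.

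**The concern.** The second part exists to ask whether people who believe they react to aspartame also report symptoms after an inert bar. That question matters most when reporters have as many symptoms on placebo as on aspartame. Yet that result is a first part with no discrimination, and the condition then sets the second part aside.

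As Study Design describes it, the first part contains reporters only, so their placebo-bar scores have no control group beside them. The second part alone supplies that comparison. It also supplies two placebo exposures in the same person, which give a period effect and a within-person repeatability SD. Both serve the stated primary purpose of testing the design and finding the power needed for a larger study, whatever the first part shows. Fifty people would complete two fasting visits with blood draws for a comparison that the plan may never make.

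**Working it through.** The protocol attaches no figure to this rule, so there is none to reproduce. The check is first one of logic, then of size.

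**1. Direction of the rule.** For a reporter, let b be the background symptom score on a test day, n the nocebo response to a blinded bar, and a the true aspartame effect.

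- Placebo bar: b + n. Aspartame bar: b + n + a.
- First-part contrast: (b + n + a) − (b + n) = a.

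Because the bars are identical and their order is randomised, n cancels on average. If a = 0, the first part is null however large n is. In the second part, with R for reporters and C for controls:

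- Reporters minus controls on placebo: (b_R − b_C) + (n_R − n_C).

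This contrast carries the nocebo information, and the rule makes its analysis depend on a quantity (a) that carries none.

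**2. Size if the trigger is a single test.** Inputs from the protocol: 50 reporters in the first part, 25 v 25 in the second, separate people, two-tailed tests. Assumed, because the protocol states none: alpha 0.05, a = 0, and standardised reporter-control differences d of 0.5 to 1.0.

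- P(second part analysed) = 0.05; P(not analysed) = 0.95.
- Power for 25 v 25 (normal approximation) = Φ(d·√(25/2) − 1.96). For d = 0.8: Φ(2.828 − 1.960) = Φ(0.868) = 0.81.
- The parts use different people, so the chance of analysing and detecting is the product: 0.807 × 0.05 = 0.04.

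| d | Analysed always | Conditional, one test | Conditional, any of 10 independent tests |
|---|---|---|---|
| 0.5 | 0.42 | 0.02 | 0.17 |
| 0.8 | 0.81 | 0.04 | 0.32 |
| 1.0 | 0.94 | 0.05 | 0.38 |

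A simulation with t-tests (20,000 runs, d = 0.8) met the condition in 5.1% of runs and detected the difference in 78.8% unconditionally and 4.1% conditionally.

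**3. Size if any of many endpoints counts.** The chance that k independent 5% tests meet the condition under a true null is 1 − 0.95^k.

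- k = 10: 1 − 0.95^10 = 0.40, so the second part is unanalysed 60% of the time (last column above).
- k = 14: ten visual analogue times (eight at 15-minute intervals over 2 hours, then 3 and 4 hours) for one item, plus insulin, glucose, GLP1 and GIP: 1 − 0.95^14 = 0.51.
- Same 14 outcomes, with an assumed correlation of 0.5, 0.7 or 0.9 among the ten times and independent blood measures: 42%, 36% or 29% by simulation.

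Steps 2 and 3 are alternative readings of one undefined phrase; their figures do not add together.

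**The case against.** **The arms might be reporters and controls.** Subject selection speaks of two groups of 50, and the title compares people with past symptoms to controls. If the arms were these groups, a difference between them would be a reasonable cue to ask about nocebo, and the rule would not work against its purpose. This cannot be excluded, but it does not fit Study Design, whose first part holds only reporters receiving both bars. The two sections need to be reconciled.

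**A reader might infer that nocebo data are discarded, or that a nocebo pattern could not be shown at all.** The text does not go that far. It states an intention, the data are collected either way, and the first part alone can show equal symptoms on both bars in 50 reporters. What is lost is the comparison with controls.

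**A reader might infer that the second part is both almost never analysed and usually analysed on a false signal.** These belong to different readings of the trigger. On the broad reading the signal need not be false: aspartame and its breakdown products are to be measured in blood and urine, so a true exposure difference could meet the condition while symptoms are identical. The numbers also rest on an assumed alpha and assumed correlations, and the protocol does not give the number of visual analogue items. Leaving trigger details to an analysis plan would be normal; the point here is the condition that the protocol itself fixes.

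**The second part helps to interpret a positive first part.** True, which is why the remedy is to analyse it always and not to reverse the condition.

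**Analysis may include assays.** Samples are stored and batched for the end of the study, and the metabolite work is subcontracted. The protocol does not give cost as the reason, but the objection is fair for laboratory measures. It does not reach symptom scores.

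**Conclusion.** The concern stands in this form: on the natural reading of Study Design, the condition works against the only stated purpose of the second part. The direction follows from blinding with identical bars and needs no numerical assumption. The illustrative size (95% unanalysed; power for d = 0.8 falling from about 0.8 to 0.04) assumes inert aspartame and one two-sided 5% test. With many eligible endpoints the loss is smaller, but whether nocebo is examined then depends largely on chance or on metabolites.

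This should be fixed, but it is not critical. Nocebo appears in none of the listed aims or endpoints. The primary endpoints concern design, power and "To study the acute effects of aspartame on psychological symptoms, biochemistry and metabonomics", and the rule biases none of those comparisons. It is also tempting to call the reporter-control difference on placebo the nocebo effect. The design does not support that: there is no occasion without a bar, so the difference also contains background symptoms, reporting tendency, and reactions to fasting or other ingredients.

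**What to change.** Delete the conditional sentence in Study Design and state that the second part's symptom data (visual analogue scales and symptom log) will be analysed whatever the first part shows. Report:

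- Reporters minus controls on the placebo bars with a 95% CI, adjusted for the baseline questionnaires already collected. Describe it as the excess of symptoms on placebo (nocebo plus reporting tendency), not as a pure nocebo estimate.
- First versus second placebo within person, for the period effect and the repeatability SD needed to plan the main trial.

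Do not set the first part's aspartame-minus-placebo difference beside the second part's second-minus-first difference unless the first part is split by sequence. The former comes from randomised order and largely balances out period; the latter is a period contrast.

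If cost is the reason for the condition, blood and urine assays in the second part may stay conditional. In that case, say so and define the trigger endpoint and the two arms before unblinding. Reconcile Study Design with Subject selection on who is in each part.

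Cost: a few more tables for symptom data and no extra data collection. Making the assays unconditional as well could add laboratory work for 50 people.
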